## Abstract

**Background:**

This randomized control trial assesses the effectiveness of motivational interviewing (MI) to encourage behavior change in new mothers relating to caries prevention when caring for their newborn American Indian (AI) infants and young AI children.

**Methods/Design:**

The study is a randomized control trial. We hypothesize that when motivational interviewing is added to enhanced community oral health education services, the new mothers will achieve greater reduction of caries experience in their AI children compared to those who are receiving enhanced community services (ECS) alone. Six hundred mothers or caregivers of AI newborns will be enrolled into the study and randomized to one of the two intervention groups over a two-year period. The children will be followed until the child’s third birthday. A cost analysis of the study is being conducted in tandem with the enhanced community services, motivational interviewing behavioral interventions, and the dental screenings for the length of the study.

**Discussion:**

The trial is now in the implementation phase and a number of threats to successful completion, such as recruitment and retention challenges in a vast, rural geographic area, have been addressed. The protocol provides a unique model for oral health interventions using principles of community-based participatory research and is currently on schedule to meet study objectives. If the study is successful, motivational interviewing intervention can be applied in AI communities to reduce ECC disparities in this disadvantaged population, with study of further applicability in other populations and settings.

**Trial registration:**

ClinicalTrials.gov,
NCT01116726.

## Background

The extensive health disparities experienced by American Indians and Alaska Natives (AI/AN) include oral diseases, such as dental caries (cavities) and periodontal (gum) disease. The United States prevalence of early childhood caries (ECC) is highest in American Indian (AI) children
[1]. ECC is defined as the presence of one or more decayed, missing, or filled tooth surfaces in any primary tooth in a preschool-age child between birth and six years of age
[2]. A recent study of oral disease on the Pine Ridge Reservation revealed that 84% of children (n = 157) had untreated decay
[3]. Early childhood caries in young children often signal the beginning of a downward spiral of increasingly poor oral health and oral health-related quality of life. A cariogenic diet and poor oral health behaviors in the first two years of life are associated with ECC.

Results from the 1991 and 1999 Indian Health Service (IHS) Oral Health Surveys, and more recent studies, indicate that ECC continues to increase in AI/AN children
[1]. When compared to other children aged two to five years, the percentage of untreated decay is more than three times higher in AI/AN children (18.7% versus 68%)
[1]. An oral health surveillance system for children aged one to five years (n = 8461) was initiated by the IHS in 2010. Overall, 54% of AI children had decay experience, 39% of children had untreated decay, and 36% needed urgent dental care. The prevalence of caries increased with age, with 21% of one-year-olds and 75% of five-year-olds having a history of dental caries
[4]. The etiology of ECC is multifactorial and determinants include social, behavioral, biological, and service system factors
[5-9]. Behaviorally–mediated risk factors which include cariogenic diet, poor oral hygiene, and unattended bottle feedings in the first two years of life are all associated with ECC
[10,11]. These oral health behaviors are related to inappropriate information, a belief that baby teeth are not important, mothers’ previous negative experiences with oral health care, and difficult experiences brushing children’s teeth
[12-14].

Motivational interviewing (MI) is a behavioral intervention approach that was first developed for use with alcohol and substance abuse populations
[15]. More recent applications have included use in a broad array of health challenges, including oral health. It involves informal assessment by the interventionist of the focal person’s stage of ‘readiness for change’ with regard to a targeted behavior
[16]. This collaborative, client-oriented approach supports participants in openly discussing concerns about, and obstacles to, changing behavior. In contrast to more direct approaches in which individuals are told how to change their behavior, MI uses techniques that elicit self-motivating statements and place the responsibility for change directly under the client’s control
[17]. This method is based on the principle that exploring and resolving ambivalence about taking action is an essential component in this preparation for change
[18-21]. A Scottish trial suggested that actions as simple as formulating an action plan with the focal participant in about one minute can generate significant changes in behavior
[22]. Another study reported that even one session of this intervention (with telephone follow-up) increased the use of fluoride varnish and consequently reduced ECC
[23].

This manuscript describes the protocol for a randomized control trial to use motivational interviewing (MI) to affect caries prevention behaviors by new mothers of AI infants and young children. The trial is being conducted by the Center for Native Oral Health Research (CNOHR) at the University of Colorado Anschutz Medical Campus (United States), which was established in 2008. It is one of five oral health disparities centers nationally, and one of three Collaborating Centers for Early Childhood Caries (other ECC centers are located at the University of California, San Francisco and Boston University).

## Methods/Design

### Study design

This study is a randomized controlled trial to determine whether behavioral intervention using motivational interviewing with AI new mothers will achieve a greater reduction of caries experience in children younger than three years than enhanced community services alone. Six hundred mothers (n = 600) or caregivers of newborns will be enrolled and randomized to one of two groups over a two-year period with a period of follow-up lasting until the child’s third birthday.

The control group will receive enhanced community oral health services only and the intervention group will receive MI plus enhanced community services. The MI intervention will consist of four visits, the first shortly after childbirth, and again when the children attain 6, 12, and 18 months of age. Enhanced community services includes the provision of oral health supplies for the child and immediate family members, informational brochures with culturally specific artwork and designs, public service announcements in the newspaper and on the tribal radio, and billboards placed in strategic locations on the reservation focusing on the important ECC risk factors. Each of the two intervention groups receives an equal number of visits across the three years of study participation. All study participants will receive financial compensation in the form of a gift card for each study session completed.

The primary outcome will be caries experience, assessed as decayed, missing, and filled tooth surfaces (dmfs) of the children at one, two and three years of age. Secondary outcomes will include caries patterns, costs, dental knowledge, attitudes, and oral health-related behaviors of children and mothers or caregivers assessed at baseline, one, two, and three years.

### Conceptual framework

Figure 
1 presents the conceptual framework that guides the study. The framework combines key variables specified in health behavior theory with constructs shown in the literature to be influenced by MI. Each session is conducted within the ‘spirit of MI’, which means the session is collaborative, calls forth or evokes information and motivation from within the participant, and honors the patient’s autonomy to decide what is best for her or him. We hypothesize that MI will lead to positive behavior change (increased adherence to recommended behaviors and use of preventive care), resulting in improved oral health outcomes for the target child. Outcomes of interest include caries experience (as measured by dmfs) and perceived oral health status, as well as reports of changed oral health behaviors, and health care costs associated with dental treatment. Based on prior research examining the impact of MI, we expect that the intervention will result in improved oral health behavior through improved oral health knowledge, self-efficacy, and an increased sense of the importance of good oral hygiene. We theorize that when participants learn more about oral health during the MI sessions, they will be able to formulate oral health care goals for their children; develop the confidence and motivation for behavior change through this supportive discussions about the importance of oral health practices and formulate action steps
[24]. The participant will talk of her desires, abilities, reasons, and need for change (DARN), and is likely to arrive at a commitment to change and develop an action plan
[24,25]. Socio-demographic characteristics (such as age, education, income) will be recorded so that we can control for the potentially confounding influence of these variables. We will also collect data on a number of variables that may moderate the impact of the intervention.

**Figure 1 F1:**

**Conceptual framework for motivational interviewing and oral health outcomes.** The figure presents the conceptual framework that guides the study. This framework will guide the intervention that will impact the oral health behaviors and ultimately the oral health outcomes. dmfs, decayed, missing and filled tooth surfaces.

### Objectives

There are three specific aims of the study. The first is to collaborate with AI community service providers and residents to develop culturally appropriate educational and health promotional materials (brochures, public service announcements aired on the reservation radio station, and billboards) to emphasize the value of family oral health from birth. The second is to create a culturally specific manual for an MI intervention on oral health focusing on mothers or caregivers and their newborn and young AI children. The third is to compare the effectiveness of enhanced community services plus this MI intervention versus enhanced community services alone on the children’s dmfs measures at years one, two and three.

The secondary aims for this study are: to assess other outcome measures, including specific caries patterns and costs of the interventions; and to investigate potential moderators and mediators of the intervention conditions.

### Participants

Study participants are enrolled at the Pine Ridge IHS hospital, powwows, health fairs, local community events, and in Rapid City, South Dakota (United States).

### Inclusion criteria

The participating child must be AI, as defined by the tribe, living on or near Pine Ridge Reservation in South Dakota. The adult must be the mother or caregiver of the newborn AI child, be between 15 and 65 years of age (in the case of minors who are 15 to 17 years of age, consent also is obtained from a parent or legal guardian according to Tribal, State, and IHS rules and regulations), be able to understand and sign a consent form, and be willing and able to follow study procedures and instructions. Mothers or caregivers of twins are included, but only one child will be included in the study, as selected by the mother or caregiver. Fathers are included as members of the larger family setting, but are not the focal point of the intervention. In situations where the father is the primary caregiver; he and his child are eligible for the study.

### Exclusion criteria

Any persons who are not mothers or caregivers of AI children, persons without responsibility to care for a newborn AI child, and parents or caregivers under the age of 15 or over the age 65 are not eligible for this research study. Newborns with serious congenital syndromes expected to adversely affect the development of primary teeth are excluded. This does not include children with cleft lip or palate; these children are not automatically excluded. Participants are also excluded if they cannot understand and sign a consent form, and are not able to follow study procedures and instructions.

### Study site

The trial is being conducted on the Pine Ridge Reservation of the Oglala Sioux Tribe (OST), the second largest reservation in the United States, covering an area of 4,353 square miles. Approximately 32,000 people live on the reservation, often in small, isolated communities and rural clusters. The Pine Ridge Reservation has an unemployment rate of 89% which leads to marked poverty
[26]. Three Indian Health Service (IHS) dental clinics are located on the reservation, however, due to high levels of acute need professional dental staff must address these acute problems, leaving little time and few personnel to focus on prevention. The Pine Ridge Reservation was selected as the site for this study because of the high need for oral disease prevention
[3], the university’s long standing working relationship with the tribe, and because it is one of the few reservations where the number of births is large enough to allow us to meet statistical power requirements for a trial of this type
[27].

### Intervention

#### Motivational interviewing (MI)

A culturally specific MI script was developed with a Native MI consultant, a training manual was compiled, intervention providers were trained, and a pilot test was completed before the MI intervention was used in the field. The intervention providers are local people with some education beyond high school, no oral health training or experience but with experience working in a position with public interaction. The two day training for the intervention providers includes MI material written by the Native MI expert with emphasis on integrating AI and western practices providing the foundation for MI with AI populations
[28]. They learn and demonstrate the use of communication skills to work with people as partners as they consider personal behavior change. They practice fundamental MI techniques that focus on helping clients strengthen the motivation to improve oral health behaviors. During training, the intervention providers conduct five audio-recorded practice sessions of mothers or caregivers for review and feedback by the MI intervention director in consultation with the MI consultant. Once the intervention providers are fully trained they will start intervention visits. However, every intervention will be recorded and a fidelity measurement will be conducted (discussed below).

Participants will choose the location where they meet with the MI intervention provider. A participant may choose to meet at their home, in a common public place (such as a local library in a private room), at the field office, or another community program location. Whenever possible, the same intervention provider will meet with the same study participant for each of the four interventions. At each MI intervention visit, the date of the visit, age of the child, content selected for discussion, the mother or caregiver’s decisions regarding next steps, their satisfaction with the visit, and oral health supplies left with the family will be recorded. The MI intervention providers will also record missed visits and all attempts to schedule visits.

#### Measurement of fidelity

All MI sessions are to be audio-recorded, as required for intervention fidelity monitoring by the NIDCR. Ongoing monitoring is to include a review of a random sample of 20% of the intervention recordings, scoring them against the Motivational Interviewing Treatment Integrity (MITI)
[29]. Intervention providers will be given feedback on the audited intervention sessions, with special attention to adherence to the MI model and competence in the use of MI. Intervention providers will participate in self-reflection on their adherence and competence as part of the supervision and feedback sessions. For purposes of inter-rater reliability, half of the random sample of sessions selected for review will be rated a second time with the MITI by the MI consultant (10%).

#### Enhanced community services (usual care)

Development of enhanced community services includes text for public service announcements, billboards, recruitment flyers, as well as tri-fold brochures focusing on behavioral risk factors for ECC and oral health topics covered in the MI sessions. Additionally, toothbrushes and toothpaste are given to the participant.

### Primary outcome measure

The dmfs index measures the level of dental caries, the primary outcome measure. The caries experience for a child is expressed as the total number of teeth or surfaces that are decayed (d), missing (m), or filled (f). Study-trained and calibrated licensed dental hygienists blinded to the study condition will conduct visual examinations of the enrolled children’s mouths at aged one, two and three years to determine dmfs, and trained study personnel record the observations. The caries evaluation will be performed annually for three years for several reasons: more frequent contact with the participant may increase the likelihood that the participant will remain in the trial; measuring the outcome at three different time points should potentially increase the likelihood of obtaining useful data, even if the participant misses one or more of the follow-up visits; and multiple assessments of the outcome will increase the statistical power of the final analysis of the trial.

A knee-to-knee examination is completed with the assistance of parents or caregivers. The child’s teeth are brushed to enable adequate visualization of tooth surfaces and a direct light source and mouth mirror are used to systematically evaluate each tooth for the presence of decayed and filled surfaces. Caries detection and measurement criteria as described by Pitts are used to visually evaluate and score lesions
[30,31]. The findings are charted in an electronic dental research record called CARIN (Caries Research Instrument)
[32], which is used across all three Early Childhood Caries Centers funded by NIDCR.

### Secondary outcome measure

To capture information about parents’ oral health knowledge, attitudes, and behaviors, a parental oral health survey, the Basic Research Factor Questionnaire (BRFQ) was developed. The BRFQ development was a collaborative effort involving the three Collaborating Centers for Early Childhood Caries funded by NIDCR.

Constructs included in the Basic Research Factors Questionnaire

Constructs

Parent and Household Characteristics

Age

Gender

Highest Grade

Employment Status

Ethnicity

Race

Tribal Affiliation

Relationship to Child

Number of Household Members

Annual Household Income

Perceived Adequacy of Income

Child Socio-demographics

Ethnicity

Race

Tribal Affiliation

Age

Child’s Dental Health

Child’s Oral Health Status

Child’s Oral Health Quality of Life

Dental Insurance Coverage

Dental Care Utilization (Preventive and Restorative Care)

Time and Travel Costs (e.g., Missed Work Due to Child Dental Care)

Oral Health Knowledge & Behavior

Oral Health Knowledge

Oral Health Behavior

Oral Health Attitudes

Self-efficacy (Confidence that One Can Engage in Good Oral Health Behavior)

Perceived Importance of Good Oral Health Behavior

Locus of Control Regarding Child’s Oral Health

Perceived Benefits of and Barriers to Good Oral Health Behavior

Perceived Seriousness of Poor Oral Health Outcomes for Child

Perceived Susceptibility of Child to Poor Oral Health Outcomes

Parental Resources, Barriers, and Health Status

Health Literacy

Comorbidities

Parent’s Oral Health Status

Alcohol Use

Distress

Chronic Stress

Perceived Discrimination

Tribal Identity

Sense of Coherence

Social Support

Access to a Working Vehicle

The BRFQ was designed to be administered using an audio computer-assisted self-interviewing (ACASI) system. The survey was programmed in SSI Web from Sawtooth Software
[33] and is implemented on encrypted Dell Inspiron Mini laptop computers, Dell, Texas, United States

### Randomization

A stratified blocked randomization was developed by CNOHR biostatistical staff using a random number generator. Randomly selected block sizes of 2 and 4 are used. Blocked randomization of randomly selected sizes is used to prevent the field staff from knowing what treatment the next participant will receive during the recruitment process and to ensure that if the study is stopped at any particular time there will be an approximately equal number of participants in each study arm. Stratification is based on age of mother or caregiver. Randomization is completed over the phone between the field staff enrolling the participant and a staff member at University of Colorado Anschutz Medical Campus. The field staff is required to obtain consent and enroll the subject in the trial prior to seeing the group assignment.

### Blinding

Due to the nature of the interventions, the intervention providers and participants cannot be masked in this study. However, the licensed dental professionals who perform the annual oral health screenings are blinded to group assignment.

### Sample size

Based on the IHS 1999 dental survey of the AI population
[1], the mean dmfs for all AI nationally was 10.05 (SD = 16.27) at age two and 12.22 (SD = 19.17) at age three. Assuming a repeated measures analysis with dmfs measured at 3 time points (years one, two and three), an intra-class correlation of 0.50, a 40% reduction in mean dmfs due to the MI intervention, a 90% statistical power using an α = 0.05 2-sided test, and an 80% retention rate, we arrived at a total sample size of 540 mothers and newborns in the two treatment arms (270 per arm). The final target sample size was set at 600 to allow for some potential misspecifications of the statistical assumptions.

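### A common intra-class correlation of 0.50 conflicts with the plan's own age-two and age-three dmfs figures, so the one-third saving credited to repeated measures is not supported as stated

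*Protocol article*

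**What the plan says.** The Sample size section takes its planning values from a national survey: "the mean dmfs for all AI nationally was 10.05 (SD = 16.27) at age two" and "12.22 (SD = 19.17) at age three". It assumes "a 40% reduction in mean dmfs due to the MI intervention", 90% power, a two-sided 5% test and 80% retention. For the repeated measures it states: "Assuming a repeated measures analysis with dmfs measured at 3 time points (years one, two and three), an intra-class correlation of 0.50". It gives no source for 0.50 and no mean or SD at age one. The result is 540 in total (270 per arm), raised to a target of 600 as a margin for misspecified assumptions.

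The Primary outcome measure section defines dmfs as a total of decayed, missing and filled surfaces. Among its reasons for annual examinations it states that "multiple assessments of the outcome will increase the statistical power of the final analysis of the trial". The Analyses section plans linear mixed models, with the covariance structure chosen from the data.

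**The concern.** dmfs is a running total. Once a surface is decayed, missing or filled it normally stays in the count, so a child's age-three value is the age-two value plus an increment of zero or more. Running totals from adjacent years tend to be strongly correlated, and a later measurement then adds little information. The sample size nevertheless relies on a moderate correlation, and that one input is responsible for a third of the reduction in N. If the correlation is too low, the stated 90% power is too high, and a null result would be less informative than the plan implies. The question is whether 0.50 is merely optimistic or actually conflicts with the means and SDs printed beside it.

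**Working it through.** **Inputs** (all from the Sample size section): age two, mean 10.05 and SD 16.27; age three, mean 12.22 and SD 19.17; 40% reduction; z-values 1.960 + 1.282 = 3.242; retention 80%; three visits; correlation 0.50.

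**1. Reproducing 540.** The section prints no formula. The following one gives its figure.
- Difference at age three: 0.40 × 12.22 = 4.888.
- Single measurement, per arm: 2 × (19.17 × 3.242 / 4.888)² = 323.2. Divided by 0.8 this is about 404, or roughly 810 in total after rounding up.
- Repeated-measures factor with common correlation ρ: (1 + 2ρ)/3 = (1 + 2 × 0.50)/3 = 0.667.
- 323.2 × 0.667 = 215.5; divided by 0.8 this is 269.4, so 270 per arm and 540 in total.

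With age-two inputs the same formula gives 574. The 540 therefore corresponds to the age-three mean and SD used at every visit.

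**2. What the quoted moments imply for ages two and three.** Write Y3 = Y2 + I, with Y2 ≥ 0 and I ≥ 0.
- E[I] = 12.22 − 10.05 = 2.17.
- Cov(Y2, Y3) = 16.27² + Cov(Y2, I) = 264.7 + Cov(Y2, I).
- SD product: 16.27 × 19.17 = 311.9.
- A correlation of 0.50 needs Cov(Y2, I) = 0.50 × 311.9 − 264.7 = −108.8.
- Because Y2 × I is never negative, Cov(Y2, I) ≥ −E[Y2] × E[I] = −10.05 × 2.17 = −21.8.
- Minimum correlation: (264.7 − 21.8)/311.9 = 0.779.
- If the increment is uncorrelated with earlier dmfs: 16.27/19.17 = 0.849.

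No assumption about the number of tooth surfaces is needed.

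**3. Effect in the formula of step 1.** For unequal pairs, ρ is the mean of the three pairwise correlations.

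| Correlations | ρ | N for 90% power | Power at 540 | Power at 600 |
|---|---|---|---|---|
| As stated | 0.50 | 540 | 90.1% | 92.8% |
| 0.50, 0.50, 0.779 | 0.593 | about 589 | 87.4% | 90.5% |
| 0.50, 0.50, 0.849 | 0.616 | about 602 | 86.7% | 89.9% |
| Common 0.779 | 0.779 | 690 | 81.9% | 85.7% |
| Common 0.849 | 0.849 | 728 | 79.8% | 83.8% |

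A target of 600 keeps 90% power up to a mean correlation of about 0.61.

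**4. Ages two and three alone, each with its own mean and SD** (average of the two visits).
- Difference: 0.40 × (10.05 + 12.22)/2 = 4.454.
- Variance of the average: (16.27² + 19.17² + 2ρ × 311.9)/4 = 279.5 at ρ = 0.779 and 290.4 at ρ = 0.849.
- Total N = 2 × 2 × variance × 3.242² / 4.454² / 0.8, or about 740 and 770.

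Optimal weighting of these two visits hardly changes this (about 740 and 768).

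**5. Adding age one, by assumption.** With an assumed age-one mean of 0.5 to 3, SD 1.6 to 2.5 times the mean, 0.50 for the age-one pairs and 0.75–0.85 for ages two/three (the lower end is just under the floor from step 2), a simple three-visit average needs about 665–765. Optimal weighting for a common 40% reduction needs about 597–760. With age-one correlations of 0.2–0.3, optimal weighting needs about 473–699.

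**The case against.** **Only one pair is bounded.** This stands. A single intra-class correlation summarises three pairs. Without age-one moments, those pairs could lie below 0.50 and the average could be close to it. A reader might infer that 0.50 is impossible as an overall value, or that the trial needs 690 to 728 children; the document supports neither. The second inference puts the age-two/age-three floor into pairs about which nothing is stated.

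**The 600 target already allows for misspecification.** This largely stands if the age-one pairs are at 0.50: power at 600 is then about 90%. The margin is used up by this one input, however, and it is not enough if all pairs are as high as 0.78.

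**A mixed model with a data-driven covariance may do better than a simple average.** It may. Step 5 shows that favourable age-one values could bring the requirement below 540. The article states no such values, and the reproduced calculation uses age-three figures at every visit. The larger requirements in steps 4 and 5 also reflect the change of means and SDs, so they do not measure the correlation error alone.

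**The survey is cross-sectional and examinations contain error.** The 2.17 is a difference between survey age groups, presumably of different children, so the bound is conditional. Scoring error could lower the observed correlation. To reach 0.50, though, the true age-two variance could be at most 0.50 × 311.9 + 21.8 = 177.8. That is a reliability of 177.8/264.7 = 0.67 (0.59 if increments are uncorrelated with earlier dmfs), which is low for calibrated examiners.

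**A condensed article may omit the justification.** The missing source is therefore not the point. The conflict is between figures that the section does print.

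**Conclusion.** The point holds for the age-two/age-three pair. With the quoted moments as planning values and a count that does not fall within a child, the correlation is at least 0.78, and about 0.85 if increments are unrelated to earlier disease, against the 0.50 applied to all pairs. The arithmetic of 540 is correct; the input is not consistent with the figures beside it, and the one-third saving is not supported as stated.

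The size of the loss is not determined by the document. In the plan's own formula, power at 600 runs from about 90–91% (age-one pairs kept at 0.50) to 84–86% (0.78–0.85 throughout). At 540 the corresponding figures are about 87% and 80–82%. The formula itself is inferred from its exact agreement with 540. This is a planning input to correct and a power statement to restate; it does not show that 600 is inadequate.

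**What to change.** In the Sample size section, replace the single intra-class correlation with a mean and SD for each age and three pairwise correlations. Take 0.78–0.90 for ages two and three. Label the age-one mean, SD and correlations as assumptions and show a range for them. Recompute under the planned linear mixed model and restate the power for the fixed target of 600 across that range. As an optional check, compare the values with the variances and correlations of children already examined, pooled over arms without unblinding.

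The cost is a recalculation and revised wording. The stated power may become less favourable; enrolment does not change.
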